**Hours of use**															
**Amount of tablets (paracetamol)**															
**DATE**	/	/	/	/	/	/	/	/	/	/	/	/	/	/	/
**Hours of use**															
**Amount of tablets (paracetamol)**															

**INSTRUCTION:** At the end of every day, you must write down the total amount of hours that you used the Moleca and the number of paracetamol tablets taken (take only if you feel knee pain).

Process B consists of an anamnesis specific to knee pain symptoms at night, while standing, and during locomotion, using a VAS. Musculoskeletal function is analyzed by a six-minute walk test [27], the Western Ontario and McMaster Universities Osteoarthritis questionnaire (WOMAC) [28] and the algofunctional Lequesne Index of severity of OA [29]. All patients are assessed according to Process B at baseline, after three months of intervention, and at the end of six months intervention, by PT 2. The WOMAC questionnaire assesses three dimensions: pain, disability, and joint stiffness in knee OA, and it is refering to 72 hours prior to the evaluation, using a 24-question, 5-point Likert protocol. The higher the score, the worse is the condition [28]. The Lequesne questionnaire assesses pain or discomfort, maximum distance walked, and activities of daily living, 72 hours prior to the evaluation [29]. The higher the score, the worse is the condition. The six-minute walk test [27] is a practical, simple test that measures the distance that a patient can quickly walk on a flat, hard, indoor surface in a period of six minutes. This test evaluates the patient's ability to perform daily living activities. We strictly followed the American Thoracic Society guidelines when conducting this test [27].

Process C consists of a biomechanical gait analysis; the inverse dynamic approach is employed to calculate KAM. Patients of both groups are assessed at the baseline and at the end of six months. We use three-dimensional displacement of passive reflective markers (20 mm in diameter), tracked with six infrared cameras (OptiTrack FLEX: V100; Natural Point, Corvallis, OR, USA) [20] and ground reaction forces acquired by a force plate (AMTI OR 6–7 1000, Watertown, MA, USA) embedded in the centre of a 10-meter walkway. The reflective markers are placed on the subject using a standard Cleveland Clinic marker set [30]. Extra markers are placed bilaterally at the medial knee joint line, medial malleolus, and first metatarsal joint for the static standing trial, in order to determine relative joint centres of rotation for the knee, ankle, and longitudinal axis of the foot. These extra markers are removed in the gait trial. In addition, two sets of technique clusters are placed in the lateral thigh and over the shank. Marker placement is performed by the same physiotherapist who performs the blind assessment (Processes B and C). We evaluate the limb correspondent to the symptomatic knee in subjects with unilateral OA and the most symptomatic knee in subjects with bilateral OA [17,18].

The laboratory coordinate system is established at one corner of the force plate, and all initial calculations are based on this coordinate system. Each lower limb segment (foot, shank, and thigh), based on surface markers, is modelled as a rigid body with a local coordinate system that coincides with the anatomical axes. Translations and rotations of each segment are reported relative to neutral positions defined during the initial standing static trial. The inertial properties are based on Dempster’s standard regression equations. The moment of inertia and location of centre of mass are computed assuming the thigh and shank segments as a cylindrical geometric shape. The knee is examined as a bicondylar type joint with biplane movements; flexion/extension, adduction/abduction (in smaller range of motion) andmedial and lateral axial rotation [31].

Force and kinematic data acquisition are synchronized and sampled by an A/D card (AMTI, DT 3002, 12 bits) at 100 Hz. We use the Visual3D software (C-motion, Kingston, ON, Canada) and a custom-written Matlab function (MathWorks, Natick, MA, USA) to perform all mathematical procedures.

### Outcome measures

The primary outcome measure is the pain WOMAC score (Table 2), based on the OARSI task force [32].

**Table 2 T2:** Outcome measures

**Primary Outcome**	**Measurement**
Pain subscale	WOMAC osteoarthritis score
**Secondary Outcomes**	
- Stiffness and disability subscale	- WOMAC osteoarthritis score
- Knee pain	- Visual Analogue Scale (0–10 cm)
- Function and progression of OA	- Lequesne’s algofunctional questionnaire score
- Six-minute walk test result	- Distance (m)
- Paracetamol (500 mg) intake	- Days and amount of paracetamol ingested over six months
- Knee load during gait	- Knee adduction moment (%body weight/height) by inverse dynamics during gait
- Global medical assessment	- Ordinal scale (1-much worse, 2-slightly worse, 3-no change, 4-slightly better, 5-much better)
- Global patient’s self-assessment	- Ordinal scale (1-much worse, 2-slightly worse, 3-no change, 4-slightly better, 5-much better)

The secondary outcomes are: total WOMAC score; joint stiffness and disability WOMAC subscale scores; knee pain symptom on movement, at rest, and at night with a VAS; walking distance in the six-minute walk test; Lequesne score; intake of paracetamol (500 gm) (number of days and quantity) over six months; knee load during gait; global medical assessment score; and global patient self-assessment score (Table 2).

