Although it is reasonable to suppose a therapeutic effect of flexible, minimalist, and inexpensive shoes in the treatment of knee OA, its efficacy in reducing pain and KAM, as well as recovering musculoskeletal function in elderly people with knee OA has not been tested yet through a randomized, controlled trial. If effective, the use of these inexpensive, minimalist shoes might be part of a treatment prescription, representing a way of reducing costs associated with OA patients’ treatment.

Our hypothesis is that the use of the intervention footwear by elderly women with knee OA for at least six hours per day for six months could (i) relieve knee pain; (ii) improve musculoskeletal function in daily living activities; (iii) reduce knee load during gait; and (iv) reduce the use of medication, and, therefore, could be considered another inexpensive option for conservative OA treatment. Our aim is to investigate the therapeutic effect of inexpensive and minimalist footwear on the clinical and functional aspects of OA and gait biomechanics in elderly women with knee OA.

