## Methods/Design

### Overview of the research design

A randomized, controlled trial was designed to study the effects of the shoe intervention on knee OA. Elderly women diagnosed with knee OA are recruited from hospitals and primary care centres, and are referred to a physical therapist, who performs the group allocation. The participants then are referred to another physical therapist, who performs the initial blind assessment.

All patients allocated to the intervention group (IG) receive the minimalist footwear on the first day and have to use it for six months, for at least six hours daily. The patients allocated to the control group (CG) do not receive the intervention footwear. All patients are assessed at baseline condition, after three months, and after six months (end of intervention). During this period, they continue to receive routine analgesic medication recommended by the medical staff at the hospital.

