### Protocol assessments

Eligible patients are assessed according to Process A, which consists of an interview and a clinical examination to classify the patient’s overall health condition, performed by the rheumatologist (global medical assessment score 1–5) and by the patient (global patient self-assessment score). Full-extension anterior–posterior knee radiographs are used to confirm the OA diagnosis and classification according to Kellgren–Lawrence criteria [23]. Process A is performed by a rheumatologist who is blind to the patient’s allocation. The two overall health condition assessments are conducted at baseline and at the end of the intervention period by the same physician.

At baseline, patients from both groups receive a diary to record the amount, in hours, of Moleca® use, and the intake of paracetamol tablets (500 mg) on a daily basis. Every three months, the diaries are collected in order to account for the Moleca® and painkillers use (Table 1).

**Table 1 T1:** Diary of intervention shoe use and Paracetamol intake

**NAME:____________________________________________________________________MONTH ** – First day:_____/_____/_____Final day: _____/_____/_____															
**DATE**	/	/	/	/	/	/	/	/	/	/	/	/	/	/	/

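### No paracetamol intake is described before the shoes are given, so the planned baseline comparison cannot be made for this outcome and adjustment for usual intake is forgone

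*Protocol article*

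**What the plan says.** All references are to the protocol article.

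- **Background, fourth hypothesis:** wearing the shoe could "reduce the use of medication, and, therefore, could be considered another inexpensive option for conservative OA treatment". The Discussion repeats lower analgesic intake as an expected result if the shoe is effective.
- **Outcome measures, Table 2:** the secondary outcome is "Days and amount of paracetamol ingested over six months".
- **Protocol assessments, source of the data:** "At baseline, patients from both groups receive a diary to record the amount, in hours, of Moleca® use, and the intake of paracetamol tablets". On collection: "Every three months, the diaries are collected in order to account for the Moleca® and painkillers use".
- **Overview of the research design, start of treatment:** "All patients allocated to the intervention group (IG) receive the minimalist footwear on the first day". No run-in is described. Of all patients during the trial it says that "they continue to receive routine analgesic medication recommended by the medical staff at the hospital".
- **Sample size and statistical analysis:** the outcome measures are to be compared across baseline, three months and six months, and between groups. The sample size is 28 per arm with 10% loss allowed for. The 80% power is stated for WOMAC pain only.

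**The concern.** The paracetamol record begins when treatment begins. The content of Processes A, B and C is set out, and none of them lists paracetamol taken before entry. Yet some prior use is to be expected: entry requires knee pain of 3 to 8 on the VAS, and routine analgesics are described as continuing.

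Two things follow. First, the analysis section promises a comparison with baseline that this outcome, a total over the treatment period, cannot supply. Second, painkiller use probably differs a good deal between women and persists within a woman. If so, part of the variance of the six-month total is habit brought into the trial. A pre-treatment value would remove that part; without one it stays in the error term. With about 25 evaluable women per arm this could matter for one of the four hypotheses. A later analysis plan cannot adjust for a value that was never collected.

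**Working it through.** **1. Is there a baseline value?** The outcome window is the six months of the trial. The diary starts at baseline and is collected every three months, so it yields intake for months 0–3 and 3–6. Shoes are given on the first day. No described item covers the time before that. The baseline term of the planned comparison is therefore empty for paracetamol.

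**2. The plan's own figure.** The 56 patients are for WOMAC pain; no power, SD or effect size is given for paracetamol. One route reaches 56: a between-group repeated-measures F test with f = 0.30, three visits and a correlation between visits of 0.3.
- λ = f²·N·m / [1 + (m − 1)ρ] = 0.09 × 50 × 3 / 1.6 = 8.44. Power is 0.81 at N = 50, and 0.796 at N = 48.
- Allowing for loss: 50 / 0.9 = 55.6, so 56.

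The correlation is not stated in the article, and at 0.5 the same test needs 62 (69 after loss). None of this speaks to paracetamol.

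**3. Inputs for the paracetamol comparison.**
- From the article: 28 × 0.9 ≈ 25 per arm; α = 0.05, taken as two-sided.
- Assumed: standardised difference d = 0.6, which is the plan's f = 0.30 carried over from pain (d = 2f for two equal groups).
- Assumed and ranged: ρ, the correlation between prior and on-trial intake.

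**4. Formulas.**
- Unadjusted: noncentrality d·√(n/2) = 0.6 × √12.5 = 2.121, with 48 df.
- Adjusted for a pre-treatment value: the residual variance is multiplied by (1 − ρ²), so the noncentrality is 2.121 / √(1 − ρ²), with 47 df.

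**5. Results for d = 0.6.** Unadjusted power is 0.547.

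| ρ | Noncentrality, adjusted | Power, adjusted | Points forgone | Equivalent of 50 patients, 50(1 − ρ²) |
|---|---|---|---|---|
| 0.3 | 2.224 | 0.586 | 4 | 45.5 |
| 0.5 | 2.449 | 0.670 | 12 | 37.5 |
| 0.6 | 2.652 | 0.738 | 19 | 32.0 |
| 0.7 | 2.970 | 0.829 | 28 | 25.5 |
| 0.8 | 3.536 | 0.934 | 39 | 18.0 |

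At d = 0.3, power goes from 0.18 to 0.22 (ρ = 0.5) or 0.31 (ρ = 0.7). At d = 0.5 it goes from 0.41 to 0.52 or 0.68.

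**6. Covariate, not change score.** A simple change score has variance 2(1 − ρ) relative to the six-month value alone. At d = 0.6 its power is 0.547 at ρ = 0.5, which is no gain, and 0.420 at ρ = 0.3, which is a loss.

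**7. Skewed counts.** Tablet counts are not normal, so a simulation was also run. All its inputs are assumptions: 25 per arm, a mean of 0.5 tablets a day, between-woman CV of 1, a 7-day prior count, lognormal drift between prior and on-trial use, and analysis of log(total + 1) with and without the log prior count. For a true 40% reduction:
- drift SD 0.4: power 27% unadjusted, 57% adjusted;
- drift SD 0.8: 24% and 37%;
- drift SD 1.2 plus recall error of log SD 0.5: 18% and 22%.

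With no true effect and drift SD 0.4 to 0.8, the rejection rate was 4.8% to 5.7%.

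**The case against.** The strongest reply is that this is an absence in a journal article. Process A includes an interview, and the rules on when NSAIDs and DMARDs were started imply that some medication history is taken; the full protocol may hold more. That is fair, and the point is limited to what is described. But the article does fix the outcome window, the start of the diary and a comparison that includes baseline, and these do not fit together for paracetamol. Nor does it say that the medication history counts paracetamol tablets.

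A second reply is that the outcome is sound as defined: both arms keep the diary, and randomisation makes the comparison of six-month intake fair. This stands in full. The fourth hypothesis can be tested as a between-group difference without any baseline.

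Three stronger readings are tempting and not supported:

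- A reader might infer that a chance excess of heavy users in one arm would pass as a shoe effect. That is ordinary sampling error, already covered by the 5% level, and the null simulations show no meaningful inflation.
- A reader might infer that most of the power is lost. The documents give no correlation, SD or effect size for paracetamol. The loss is small at ρ = 0.3 and becomes large only from about 0.6.
- A reader might infer that the covariate rescues this outcome. With substantial drift, power for a 40% reduction stays low even after adjustment, because the arms are small and the counts skewed.

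The hypothesis is also worded as a possibility, and paracetamol is one of many secondary outcomes.

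**Conclusion.** The point holds in a limited form. No pre-treatment paracetamol intake is described, so the announced comparison with baseline cannot be made for this outcome, and adjustment for usual intake is given up. The between-group test remains valid and unbiased; the cost is precision, and the ability to describe a reduction from a woman's usual use.

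The size is conditional: about 4, 12 or 28 power points at ρ = 0.3, 0.5 or 0.7, given d = 0.6, 25 per arm and normal theory. Both d and ρ are assumptions. The direction is firmer than the size: adjustment raised power in every non-null scenario examined, though by only a few points in the least favourable ones. This is an inexpensive improvement to a secondary outcome and does not touch the primary analysis.

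**What to change.** 1. In the Process A eligibility interview, held by the blinded rheumatologist before allocation, ask how many paracetamol 500 mg tablets were taken in the last 7 days and on how many of those days. The physiotherapist's baseline assessment is less suitable, because the design overview places it after allocation.
2. Compare six-month intake between groups on a log scale or with a log link, adjusted for that value. Do not use a simple change score.
3. For women already enrolled without the value, keep them in the analysis with a missing-covariate indicator.
4. State in the statistics section that the baseline comparison applies to paracetamol only through this value.

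The cost is one interview question for the remaining women and one covariate. The downsides are recall error over 7 days and missing values for women enrolled since March 2011, so the gain will be smaller than the table suggests. No treatment or clinical rule changes.

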### Sample size and statistical analysis

The sample size calculation was made based on the achievement of a minimal clinically meaningful improvement [33] using an effect size of 0.30 (moderate effect size), considering the pain WOMAC score as primary outcome measure. We took the SD estimates from a study we had previously completed, in which we recruited a similar patient cohort [18]. A sample size of 56 patients is needed to provide 80% power to detect a moderate effect difference between the highest and lowest group pain means, assuming an alpha level of 0.05 and a statistical design of F test of repeated measures (between and within effects), and assuming a 10% loss to follow-up. Twenty-eight patients will be allocated to each group. The statistical analysis will be based on intention-to-treat analysis, and general linear models of analysis of variance for repeated measure will be used to detect treatment–time interactions (α = 5%). The outcome measures will be compared among baseline, three months, and six months, and between groups. The expected treatment effect is a difference of 20% between groups in the percentage of patients improved, using the WOMAC score [34].

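### The three-visit repeated-measures rule does not fit the global change ratings, the paracetamol totals or the knee adduction moment, and the VAS pain items are listed in two different ways

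*Protocol article*

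**What the plan says.** All references are to the protocol article.

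- **Analysis rule** (Sample size and statistical analysis): "The outcome measures will be compared among baseline, three months, and six months, and between groups". The model is a repeated-measures analysis of variance that tests treatment-by-time interactions at the 5% level. No outcome is exempted.
- **Global assessments, by physician and by patient** (Outcome measures, Table 2): "Ordinal scale (1-much worse, 2-slightly worse, 3-no change, 4-slightly better, 5-much better". Their timing is under Protocol assessments: "The two overall health condition assessments are conducted at baseline and at the end of the intervention period by the same physician". The same section presents the score as a way to classify the patient's general state of health.
- **Paracetamol** (Table 2): "Days and amount of paracetamol ingested over six months". The diary is handed out at baseline and collected every three months (Protocol assessments).
- **Knee adduction moment (KAM)**, Process C (Protocol assessments): "Patients of both groups are assessed at the baseline and at the end of six months".
- **Pain VAS**: Process B records "knee pain symptoms at night, while standing, and during locomotion, using a VAS", whereas the list of secondary outcomes under Outcome measures names "knee pain symptom on movement, at rest, and at night with a VAS".
- **Three-month visit** (text under Figure 1): Process B only.

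**The concern.** One analysis rule is stated for outcomes that are not all collected on the schedule it presumes, and one of the scales has no meaning at the first visit.

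The global assessments matter most. A rating that runs from worse through unchanged to better needs a reference state. At six months that is the start of the trial. At baseline none is defined. If the rule is followed literally, the analysis contrasts a six-month change rating with a baseline number that rates nothing.

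Paracetamol bears on the fourth stated hypothesis, reduced use of medication. It has no baseline to compare with, and as a raw six-month total it depends on how long the patient was followed. KAM is the secondary outcome that the Discussion singles out, and it has no three-month value. For the VAS, a reader cannot tell whether the third pain condition is standing or rest.

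If this is left as it stands, the analysis of these outcomes would have to be chosen later, possibly with data in view.

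**Working it through.** **Step 1. Set the schedule against the rule.** The article's only planning figure, 56 patients, concerns WOMAC pain and does not enter this check.

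| Outcome | Baseline | 3 months | 6 months |
|---|---|---|---|
| WOMAC, Lequesne, six-minute walk (Process B) | yes | yes | yes |
| VAS at night and on movement (Process B) | yes | yes | yes |
| VAS, third condition | standing under Process B, rest in the outcome list | same | same |
| KAM (Process C) | yes | no | yes |
| Global assessments (Process A) | scored, but without a reference state | no | yes |
| Paracetamol | none: the diary starts here | a three-month total could be formed | a second three-month total, or the six-month total |

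The rule fits the first two rows fully.

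**Step 2. Global assessments: cost of using the baseline rating.** Let Y0 and Y6 be the two ratings, with standard deviations s0 and s6 and correlation r. With two visits, the treatment-by-time interaction compares Y6 − Y0 between arms, and

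Var(Y6 − Y0) = s6² + s0² − 2·r·s0·s6.

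The article gives none of these values. Assume r = 0, since a rating without a reference state should not predict later change. The standard error relative to a six-month comparison is then √(1 + s0²/s6²):

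- s0 = 0 (everyone scored 3 at baseline): √1 = 1.00, an inflation of 0%.
- s0 = s6/2: √1.25 = 1.12, about 12%.
- s0 = s6: √2 = 1.41, about 41%. The variance doubles, so 28 per arm carries the information of 14.

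If the baseline rating is unrelated to treatment, as randomisation implies, its expected value is the same in both arms. The contrast then still estimates the six-month difference: precision is lost, but no bias arises.

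**Step 3. Paracetamol: effect of early exit on a raw total.** Suppose a fraction p of an arm leaves at month t and each patient's daily intake is constant and unrelated to leaving. The arm's mean total falls by the fraction p·(1 − t/6).

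- p = 10% of an arm, t = 3: 0.10 × 0.5 = 5% lower.
- The same p and t in both arms: both means fall by 5%, their ratio is unchanged, and no spurious difference appears.

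The article gives a 10% loss overall, with no split by arm and no timing, so the size and direction of any bias are unknown.

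**Step 4. KAM.** With two visits the interaction F test has one numerator degree of freedom and equals the square of the two-sample t statistic on change. It is valid. With equal variances at both visits and within-patient correlation r, change has variance 2s²(1 − r), and analysis of covariance on baseline leaves s²(1 − r²). The ratio of the second to the first is (1 + r)/2, which is at most 1. Covariance adjustment is therefore a possible gain in precision, not a correction.

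**Step 5. VAS.** Each list has three conditions. Night matches night, and locomotion matches movement. Standing and rest are left over and are not the same condition.

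**The case against.** The best defence is that the comparison sentence is a one-line summary. The article openly gives each outcome's schedule, so a reasonable reader would compare each outcome at the visits where it is collected. A journal article may also leave count models, truncated diaries and ordinal methods to an analysis plan that is not shown here. And the primary outcome is untouched.

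Much of this stands, and it rules out several stronger readings:

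- *KAM cannot be analysed as planned.* Not supported: a two-visit treatment-by-time analysis can be run and is valid. Only the three-visit sentence does not apply.
- *The global results will be biased, or the standard error will rise by 41%.* Not supported: an uninformative baseline adds noise, and 41% is the upper end of a range that starts at 0%.
- *The medication result is biased.* Not supported: that needs loss, or its timing, to differ between arms, and the article does not say that raw totals from early leavers will be used. Nor does it say that many patients will take no tablets.
- *Pain at rest is not collected.* This goes too far: rest is not among the items listed under Process B, which may be a slip of wording.

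The defence does not remove three things. The change anchors and the baseline scoring are both stated, and the stated rule joins them. Paracetamol has no baseline value under any reading. The two VAS lists differ. These are faults in what the article says, not in what it omits.

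**Conclusion.** The point holds for secondary outcomes only.

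- **Global assessments:** a change rating at baseline has no reference state, so an interaction measured from it is not interpretable. The cost is lost precision, between 0% and about 41% on the standard error. This assumes a baseline rating that is unrelated to both treatment and the six-month rating, with variance no larger than at six months.
- **Paracetamol:** a comparison with baseline is impossible, and a raw total depends on follow-up time. The size of any bias is unknown; it arises only if loss or its timing differs by arm.
- **VAS:** two passages conflict on one of three conditions. No size applies.
- **KAM:** the three-visit sentence does not apply, but the two-visit analysis is sound.

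WOMAC pain belongs to Process B and is collected at all three visits. Neither it nor the sample size is affected.

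**What to change.** 1. **Global assessments.** Do not use a baseline change score. Compare the six-month ratings between arms with an ordinal model (proportional odds) or a rank test (Wilcoxon rank-sum). If current status is what is meant, replace the change anchors with status anchors and use them at both visits.
2. **Paracetamol.** State that tablets and days of intake are compared between arms per observed diary day, with no baseline term. This removes the dependence on length of follow-up. It does not correct for leavers whose intake differs from that of patients who stay.
3. **VAS.** Make the three conditions identical under Process B and in the outcome list before any analysis, according to what the form actually records.
4. **Comparison sentence.** Limit the three-visit comparison to Process B outcomes and state that KAM is analysed at baseline and six months. Analysis of covariance on baseline KAM is optional.

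The cost is wording, plus possibly one VAS item or revised anchors on a form. No visits or patients are added. The article reports that recruitment was still open, so the changes can be fixed before unblinding. If status anchors or a new VAS item are adopted, patients already assessed will lack those values at their completed visits.
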